##### Secondary Outcomes

The secondary outcomes include the following: (1) absolute change in HbA_1c_; (2) changes in BMI, waist circumference, fasting blood glucose, and fasting lipid panel (total cholesterol, low-density lipoprotein cholesterol, high-density lipoprotein cholesterol, and triglycerides) at the end of the study compared to baseline readings; (3) to describe the rate of fasting, rate of hypoglycemia, frequency of blood glucose monitoring, and fasting experience of Muslim participants in 2024; and (4) to calculate fasting risk using the IDF-DAR score

### Data Collection, Management, and Analysis

#### Data Collection

Data for the study is collected from different channels as follows:

BruHIMS for blood test results (baseline and final), eligibility data, and medication dataBruHealth app for lifestyle data through logging and wearable data synchronized with the appHealth coach portal for eligibility and monitoring data

#### Data Security

Participant data will be captured within the HCP portal software app developed in conjunction with the DM DTx app. Data access is in compliance with the Ministry of Health regulatory requirements. The analysis will be conducted on password-protected computers.

### Statistical Analysis

Descriptive statistics will be calculated to summarize the demographic profile of the research population and the primary and secondary outcomes outlined earlier. The mean, median, SD, and IQR will be reported for continuous variables, whereas frequencies and percentages will be used for categorical variables. Depending on the distribution of independent variables, appropriate paired statistical tests, such as the paired *t* test or the Wilcoxon signed-rank test, will be used to assess statistically significant differences between outcomes before and after treatment for both primary and secondary measures. Additionally, subgroup analyses will be conducted to assess for any significant differences in primary and secondary outcomes based on patient classifications, such as BMI categories, diabetic medication use profiles, or levels of engagement with the educational modules and health coaches in the BALANCE program.

### Withdrawal

Participants are withdrawn from the study if it is deemed that continued participation in the study poses significant health risks to them. These considerations include the following: (1) participants who require hospitalization during the study period (which may or may not be related to the study), (2) those deemed by clinical investigators to require immediate adjustments to their diabetes medications as delay may cause harm, and (3) those who fail to provide 2 local emergency contacts.

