##### Escalation Model

The escalation pathway for managing participants in this study begins with a health coach assigned to the participant. Participants with hyperglycemia (defined per the study protocol) will be assigned to a dietitian or clinician in the research team for video consultation. Participants who experience (1) 2 or more episodes of hypoglycemia or (2) 3 or more episodes of hyperglycemia in a week despite dietetic interventions will be assigned to a clinical investigator for further evaluation.

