#### Outcome

##### Primary Outcome

The primary outcome is to measure the proportion of participants with a reduction in HbA_1c_ of at least 0.6% at the end of the study.

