## Results

Recruitment began on August 20, 2024, following project approval in July 2024, and continued until July 2025. By the end of data collection on November 12, 2025, a total of 459 participants had been enrolled, and 422 (91.9%) had completed the program. Data analysis is currently ongoing, with results expected in early 2026 (Figure 11).

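### Withdrawal depends partly on glycaemia and the primary denominator is not fixed, so a responder proportion among those with a final HbA1c is likely, not certain, to be too high

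*Protocol article*

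**What the plan says.** The Withdrawal section sets a general rule: "Participants are withdrawn from the study if it is deemed that continued participation in the study poses significant health risks to them". It then names three cases: hospitalisation for any cause, "those deemed by clinical investigators to require immediate adjustments to their diabetes medications as delay may cause harm", and "those who fail to provide 2 local emergency contacts". The withdrawal is from the study, not only from the programme.

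The Escalation Model section describes who reaches a clinical investigator. One route is "2 or more episodes of hypoglycemia". The other is three or more hyperglycaemic episodes in a week that persist after dietetic input.

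The Primary Outcome section defines the endpoint as "the proportion of participants with a reduction in HbA_1c_ of at least 0.6% at the end of the study". The denominator is given only as participants.

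Four other sections bear on who can be analysed:

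- Study Design schedules blood tests at baseline and at the end of the study only.
- Data Collection takes baseline and final results from BruHIMS, the national record system.
- Sample Size raises 439 to 500 to allow for 12% attrition.
- Statistical Analysis applies paired before-and-after tests to primary and secondary measures alike.

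The Results section reports that "a total of 459 participants had been enrolled, and 422 (91.9%) had completed the program".

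**The concern.** A participant whose glucose stays high despite the programme can be sent to the clinical investigator, judged to need a prompt medication change, and withdrawn. That person is unlikely to have reached a 0.6-point fall in HbA1c. If the proportion is taken among people with a final HbA1c, the participant leaves the denominator instead of counting as a failure. Missingness then depends on the outcome because of a rule in the protocol itself.

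In a two-arm trial a similar rule in both arms might partly cancel. This study has one arm, and its primary result is a single proportion, so the choice of denominator feeds directly into the headline figure. The mean change in HbA1c is exposed in the same way. The limitations paragraph in the Discussion covers volunteer sampling, lack of a control group, generalisability, short follow-up, readiness to change and digital literacy. It does not mention this selection.

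**Working it through.** **Inputs.** Enrolled 459 and completed 422 (Results). Attrition 12%, evaluable 439, target 500 (Sample Size). The documents give no response rate, so completer rates of 20 to 60% are assumed. Reasons for non-completion are not in the readable text; the flowchart (Figure 11) is not shown.

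**The plan's own figures.** 422/459 = 0.919, as stated. 439/(1 − 0.12) = 498.9, so 499, in line with the target of 500. This second figure matters here: the 439 analysed are those left after attrition, so the sample size treats non-completers as lost.

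**Which analysis the text points to.** No section states an analysis set. A paired test needs two values per person, bloods are scheduled only at the two ends, and no section keeps a withdrawn person in follow-up. Together with the attrition allowance, this points to participants with a final HbA1c. Completers (422) are used below as a stand-in for that group.

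**General expression.** Let p be the response rate in the 422 completers and q the rate in the 459 − 422 = 37 non-completers (37/459 = 8.06%). Then

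completer rate − all-enrolled rate = (37/459) × (p − q).

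The completer figure is too high when q < p and too low when q > p.

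**Ceiling, q = 0.** The all-enrolled rate is p × 422/459, so the inflation factor is 459/422 = 1.088.

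**Fewer rule-based failures.** If only f of the 37 are failures removed by the rule, comparing completers with completers plus those f people gives p − p × 422/(422 + f) = p × f/(422 + f).

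**Yardstick.** The 95% half-width is 1.96 × √(p(1 − p)/422).

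| Assumed completer rate | All-enrolled rate if none of 37 responds | Ceiling (points) | f = 20 (points) | f = 10 (points) | 95% half-width (points) |
|---|---|---|---|---|---|
| 20% | 18.4% | 1.6 | 0.9 | 0.5 | 3.8 |
| 30% | 27.6% | 2.4 | 1.4 | 0.7 | 4.4 |
| 40% | 36.8% | 3.2 | 1.8 | 0.9 | 4.7 |
| 50% | 46.0% | 4.0 | 2.3 | 1.2 | 4.8 |
| 60% | 55.2% | 4.8 | 2.7 | 1.4 | 4.7 |

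**Opposite extreme, q = 1.** At a completer rate of 50%, (211 + 37)/459 = 54.0%. The completer figure would then be 4.0 points too low.

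**The case against.** The strongest reply is that no completer denominator is stated anywhere. A condensed article commonly leaves analysis sets and missing-data handling to the full protocol or SAP, which were not available for this review. If those documents use all enrolled participants and count the withdrawn as non-responders, there is no upward bias. Completing the programme is also not the same as having a final HbA1c, since results come from the national record. This stands as far as it goes: a reader might infer that the plan excludes failures by rule, and the text does not say so. It does not dispose of the point, because the outcome-dependent removal is itself stated, and everything the article says about the analysis relies on a final value.

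A second reply concerns direction, and it stands. The Withdrawal section does not say that the medication change must be for worsening control. Recurrent hypoglycaemia also leads to the investigator, and such a participant may have a falling HbA1c. Hospitalisation may be unrelated, missing emergency contacts are an administrative matter, and participants may leave by choice. The text does not support reading most of the 37 as treatment failures.

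A third reply concerns size, and it also stands. The figures with all 37 as failures are a ceiling. A reader might take the bias to equal the sampling error. The ceiling reaches the half-width only at about 60%; at 30% it is 2.4 against 4.4 points, roughly half. No success threshold is stated for the proportion, so no declared decision would be reversed.

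Finally, filling the gaps from BruHIMS is not neutral. An HbA1c recorded after an urgent medication change may reflect the drug and would credit that effect to the programme. Whether consent covers using it after withdrawal is not stated.

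**Conclusion.** The point holds in limited form. The withdrawal rule is partly outcome-dependent, and the plan as written points to an analysis of participants with a final HbA1c. In a single-arm study that makes the primary proportion, and the mean change, likely but not certain to favour the programme. For the proportion, the inflation is at most a factor of 1.088: 1.6 to 4.8 points for completer rates of 20 to 60%, and 0.5 to 1.4 points if 10 of the 37 are rule-based failures.

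These sizes rest on assumed response rates, on treating completers as the group with a final value, and on an unknown split of the 37 by reason. An established upward bias, or an explicit rule to exclude failures, would go beyond the documents. The article describes data analysis as still under way, so the denominator can be settled before results are reported.

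**What to change.** Make these changes to the analysis plan before results are reported:

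- **Denominator.** Define it for the primary proportion as all enrolled participants with a baseline HbA1c (at most 459).
- **Non-responders.** Count as non-responders those withdrawn for hospitalisation or medication adjustment, and anyone without a final HbA1c.
- **Supporting result.** Report the completer proportion next to it, with the number of non-completers by reason.
- **BruHIMS values.** Use any HbA1c recorded near week 16 for withdrawn participants only in a sensitivity analysis, where consent allows, flagged as possibly reflecting the medication change. Keep these values out of the main mean-change analysis.
- **Mean change.** State that the main analysis describes participants with a final study value.
- **Limitations.** Add the outcome-dependent withdrawal to the list.

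The cost is wording plus, for the sensitivity analysis, a record look-up for at most 37 people. The reported proportion will be slightly lower, and it may be conservative for participants who left for reasons unrelated to glycaemia. The clinical withdrawal rule is not changed.

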### Ethical Considerations

An online participant information sheet and consent form are available on the DM DTx module in the BruHealth app. Interested individuals are required to complete the online consent form before proceeding to complete the screening questionnaire. All participants are informed that their personal information will be kept confidential and securely stored within the Brunei Health Information Management System and BruHealth platforms, which follow national data protection and privacy standards. Identifying details will not be collected or published unless doing so is essential for scientific purposes, and no identifiable information (including names, initials, or images) will appear in any reports, publications, or supplementary materials. Participants have also been informed that they may withdraw from the study at any time without any effect on their access to routine health services. Ethics approval was granted by the Ministry of Health, Brunei Darussalam Medical and Health Research Ethics Committee (MHREC/MOH/2024/111).

## Results

Recruitment began on August 20, 2024, following project approval in July 2024, and continued until July 2025. By the end of data collection on November 12, 2025, a total of 459 participants had been enrolled, and 422 (91.9%) had completed the program. Data analysis is currently ongoing, with results expected in early 2026 (Figure 11).

**Figure 11 figure11:**
[figure not shown]
CONSORT (Consolidated Standards of Reporting Trials) flowchart: the recruitment process of the BALANCE program.

## Discussion

### Anticipated Findings

With the rising prevalence of diabetes in Southeast Asia, organizations such as the International Diabetes Federation are increasing efforts in diabetes advocacy and exploring new ways to improve access to quality health care and affordable treatments. Patient empowerment by incorporating self-management represents an important component of diabetes care, which will improve health outcomes and reduce diabetes-related complications. Therefore, new interventions should be designed with a focus on incorporating the latest clinical guidelines with an all-encompassing program that includes monitoring, diabetes education, maintaining a healthy lifestyle through diet and physical activity, medication tracking, and motivational coaching. A reduction of 1% in HbA_1c_ levels over 3 months is associated with decreased mortality and a reduction in microvascular disease, while a reduction in weight has been shown to improve glycemic control and insulin sensitivity, and potentially reduce medication dosage [21,22]. Consequently, an effective program would focus on methods to improve key cardiovascular risk factors, such as a reduction in HbA_1c_ and weight.

The increasing digitalization in the health care landscape has led to the deployment of mHealth and digital interventions to guide self-management of chronic conditions, particularly in diabetes management. Diabetes management apps can supplement traditional face-to-face care. This will help reduce the time and resources required from the health care system. Patients who have better self-management practices tend to manage their condition better [9]. By allowing users to actively participate in their own health management, users can increase their health literacy and become more confident in navigating their condition. However, an issue faced by most diabetes management apps is low engagement, with many users lost to follow-up [23]. A study showed that users were less likely to engage due to the high effort and difficulty in using the apps [24]. Therefore, collecting feedback on participant experience is crucial to identify functions and protocols that need to be redesigned to create an app that enhances the patient experience and level of engagement.

Due to the global burden of diabetes, various apps for diabetes management are commercially available on the market [25]. The main functionalities offered include self-management tasks (medication, blood glucose monitoring, exercise, and food intake), weight and blood pressure tracking, and education [26]. Most apps cover at least 1 self-management task, with blood glucose monitoring being the most common function [26]. According to the research that has been conducted to assess the efficacy of these apps, diabetes self-management apps have demonstrated a significant reduction in HbA_1c_ and body weight after a 6-month follow-up [9,27]. Most of these apps are free to download, with premium functions that require additional fees. The average cost of diabetes management apps on the market is between US $4.57 and US $5.03, with a higher annual cost for apps with multiple functions, making mHealth a cost-effective solution focused on preventing disease progression [28].

DM DTx is the first digital intervention solution of its kind in Southeast Asia. Most diabetes mHealth solutions are targeted at the North American market as part of an annual subscription plan usually provided by employers. This is largely attributed to the increasing penetration of smart consumer devices and the higher acceptance of mHealth solutions in the region [28]. Additional research on the efficacy of diabetes self-management apps in Southeast Asia should be conducted, as recommendations from solutions on the market may not be suitable in Southeast Asia due to different cutoff ranges for clinical parameters and cultural differences. Lifestyle habits and user behavior may also differ vastly between different populations, solidifying the need for region-specific intervention designs. Most commercially available diabetes management apps showed only low-to-moderate success in terms of user adherence, proving that diabetes self-management solutions do not follow a one-size-fits-all approach.

This study possesses some limitations. First, the study is designed based on volunteer sampling. Ideally, the study should be designed as a randomized controlled trial to reduce selection bias and ensure that the results are generalizable to a broader population. Any observable effects cannot be conclusively attributed to the intervention due to the lack of a control group. Sampling is done within the Bruneian population, so the results may not apply to populations outside of the current demographic. As the participants are not followed long-term, there is a lack of understanding of the sustained effects and durability of the intervention over time. Participants’ readiness to change their lifestyle habits was also not measured, as it was assumed that their participation translated to readiness. Finally, participants’ digital literacy is not measured during recruitment, which may affect their participation in the digital intervention and lead to less optimal results due to external barriers.

### Conclusions

Self-management mHealth apps remain a promising adjunct to chronic disease care, especially in T2DM. However, the impact of these apps in improving health is greatly dependent on localization to a region’s clinical and cultural context. Through data-driven research, gaps in intervention and app design can be identified to bridge the gap between theorized and realized improvements in health outcomes.

Ultimately, this research aims to understand the efficacy of DM DTx to develop a solution that is fit for purpose, clinically sound, patient-centered, and sufficiently personalized.

## Abbreviations

BruHIMS: Brunei Darussalam Health Care Information and Management System
DM DTx: diabetes mellitus digital therapeutics
DTx: digital therapeutics
HbA_1c_: glycated hemoglobin
HCP: health care professional
IDF-DAR: International Diabetes Federation-Diabetes and Ramadan Alliance Risk
mHealth: mobile health
SMART: specific, measurable, achievable, relevant, and time-bound
T2DM: type 2 diabetes mellitus
